### **4.2.3 Criteria and Procedures for Participant Withdrawal**

#### **4.2.3.1 Criteria for Withdrawal**

All participants who have signed the informed consent form and successfully passed screening to enter the trial will be considered withdrawn if they discontinue the study at any time and for any reason before completing the observation period specified in the study protocol.

##### **(1) Withdrawal Determined by the Investigator**

a) Occurrence of a serious adverse event for which, in the investigator's judgment, trial participation should be discontinued;

b) Development of complications or special physiological changes during the trial that make continued participation inappropriate;

c) Poor adherence to the study protocol.

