| Control Group                    | Continuation of HF Medications                                                                                                                                                                                                                                                                                                                                                                                                                                                                                                                                                                             |
| Methods                          | Patients who have signed the Institutional Review Board (IRB) / Ethics Committee (EC)-approved Informed Consent Form (ICF) and are judged by the investigator to meet all inclusion and exclusion criteria will be enrolled into the study. Following enrollment, subjects will be randomized in a 1:1 ratio to either the intervention group or the control group. The intervention group will undergo stepwise withdrawal of HF medications, while the control group will continue the HF medications. Patients will be followed for 6 months to compare the efficacy and safety between the two groups. |
| Sample Size                      | This study requires the enrollment of 50 patients, with 25 patients allocated to each group.                                                                                                                                                                                                                                                                                                                                                                                                                                                                                                               |

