##### **(3) Handling of Withdrawn Cases**

For all withdrawn cases, the status of clinical trial completion and the reasons for withdrawal should be documented. After a participant withdraws, the investigator should make every effort to contact the participant, inquire about the reason for withdrawal, record the most recent clinical symptoms, and complete any assessments that can still be performed. If withdrawal is due to an adverse event, the investigator should provide appropriate medical management based on the participant's condition.

When a participant or their legal guardian requests withdrawal from the trial, the investigator should ask whether previously collected data may still be used for the clinical study, and the response should be documented in the raw records.

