## **5. Statistical Methods**

### **5.1 Sample Size Calculation**

This study is designed to explore the feasibility of a future large-scale trial. The sample size is set at 50 participants, based on a 2019 Lancet study investigating withdrawal of HF medications in patients with dilated cardiomyopathy.

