### **5.3.2 General Principles**

**Descriptive Statistics:** For quantitative variables, the number of observations, mean, standard deviation, median, interquartile range, minimum, and maximum will be reported. For categorical variables, counts and percentages for each category will be presented.

**Inferential Statistics:** Unless otherwise specified, all statistical tests will be two-sided, and a P-value  $\leq 0.05$  (two-sided) will be considered statistically significant. The primary endpoint was compared using the chi-squared or Fisher's exact test. Secondary endpoints were compared using Wilcoxon rank-sum test for continuous variables, and chi-squared or Fisher's exact test for categorical variables.

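### Section 4.2.3 does not separate stopping the assigned strategy from leaving the study, so an open-label investigator can end scheduled outcome follow-up before month 6

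*Protocol*

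**What the plan says.** Section 4.2.3.1 of the Protocol defines withdrawal by departure from the study. Participants "will be considered withdrawn if they discontinue the study at any time and for any reason" before their observation period is complete. Stopping the assigned drug strategy while staying under observation has no category of its own.

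Part (1) of that section gives the investigator three grounds for removal:
- The first opens "Occurrence of a serious adverse event for which" and is completed by the investigator's own judgement that participation should stop.
- The second is complications or physiological changes that make continuing unsuitable.
- The third is "Poor adherence to the study protocol", with no threshold.

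Part (3) then requires every effort at contact, a record of the reason and latest symptoms, and that staff "complete any assessments that can still be performed". It sets no visit schedule for these patients.

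Elsewhere the Protocol says that the trial is open-label and follows all participants for 6 months (4.1). Echocardiography, laboratory tests and Holter recording are monthly, and CMR and KCCQ are repeated at month 6 (4.5.1, 4.5.2). The modified intention-to-treat set leaves out patients lost to follow-up (Protocol Summary, 4.7.1), and missing data are not imputed (5.4.1). On size: "This study requires the enrollment of 50 patients, with 25 patients allocated to each group".

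**The concern.** The grounds for removal can be related both to outcome and to arm. A serious adverse event includes any hospitalisation (10.2), and heart failure hospitalisation is a component of the secondary composite (4.3.2). Adherence means opposite behaviour in the two arms: staying off drugs in one, staying on them in the other. The person deciding knows the allocation.

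If such a patient leaves the visit schedule, a deterioration that had not yet been documented may never be. The month-6 CMR, KCCQ and echocardiography may also be missing. No later analysis can recover visits that were not held, so this cannot be left to the SAP. It also weakens the claim in section 4.7.1 that the analysis approach minimises attrition bias.

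**Working it through.** **Step 1. How the Protocol treats departures from the strategy.**

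| Situation | Section | Place in the study |
|---|---|---|
| Primary endpoint reached, drugs restarted | 4.4.1 | No removal stated |
| Drugs restarted for blood pressure, glucose or ventricular rate | 4.4.3 | No removal stated |
| Atrial arrhythmia recurrence | 4.4.4 | Stays in assigned protocol, with reassessment |
| Serious adverse event, complication, poor adherence | 4.2.3.1 (1) | May be removed from the study |

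The first three rows show that a change of drugs need not mean leaving. Only 4.2.3.1 joins the two.

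**Step 2. What can be lost.** Primary criteria 1 to 3 need an echocardiogram or an NT-proBNP value, and criterion 4 needs adjudication by the research team (4.3.1). An event documented before removal counts, provided that the patient is in the analysis set. An event that would have been found at a later visit may not be.

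**Step 3. How the patient enters the analysis.** The set excludes those lost to follow-up. Section 4.2.3.1 (2) mentions loss to follow-up only under participant-initiated withdrawal, which suggests that investigator-removed patients stay in, but the Protocol does not say so. Two readings remain:
- excluded: x/25 becomes (x − k)/(25 − k);
- kept and counted event-free: x/25 becomes (x − k)/25.

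Here x is the true number of events and k the number lost undocumented.

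**Step 4. Size.** Inputs from the Protocol are 25 per arm (Protocol Summary) and the test: "The primary endpoint was compared using the chi-squared or Fisher's exact test", two-sided at 0.05 (5.3.2). The sample size itself cannot be reproduced, because section 5.1 takes it from an earlier drug-withdrawal trial without rates or power; nothing here depends on it. One patient is 1/25 = 4% of an arm.

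All event counts below are assumptions. Each cell gives the drug-withdrawal-arm rate, the risk difference in points and the two-sided Fisher p, with the k patients excluded.

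| True events, withdrawal vs continuation | k = 0 | k = 1 | k = 2 | k = 3 |
|---|---|---|---|---|
| 5/25 vs 1/25 | 20.0%; 16.0; 0.189 | 16.7%; 12.7; 0.189 | 13.0%; 9.0; 0.338 | 9.1%; 5.1; 0.593 |
| 6/25 vs 0/25 | 24.0%; 24.0; 0.022 | 20.8%; 20.8; 0.022 | 17.4%; 17.4; 0.046 | 13.6%; 13.6; 0.095 |
| 7/25 vs 1/25 | 28.0%; 24.0; 0.049 | 25.0%; 21.0; 0.049 | 21.7%; 17.7; 0.091 | 18.2%; 14.2; 0.171 |
| 8/25 vs 1/25 | 32.0%; 28.0; 0.023 | 29.2%; 25.2; 0.023 | 26.1%; 22.1; 0.044 | 22.7%; 18.7; 0.085 |
| 10/25 vs 1/25 | 40.0%; 36.0; 0.005 | 37.5%; 33.5; 0.005 | 34.8%; 30.8; 0.009 | 31.8%; 27.8; 0.018 |

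Three lost events lower the difference by between 40.0 − 31.8 = 8.2 and 20.0 − 9.1 = 10.9 points. If the patients are instead kept and counted event-free, the fall is 3/25 = 12 points whatever x is. For 7/25 vs 1/25 the withdrawal arm becomes 4/25 = 16%, and the difference 16 − 4 = 12 points instead of 24.

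**Step 5. Direction.** Take 7/25 vs 1/25 again. If the one continuation-arm event is lost and that patient excluded, the difference is 7/25 − 0/24 = 28 points instead of 24. If three event-free patients are removed from the withdrawal arm and excluded, it is 7/22 − 1/25 = 31.8 − 4.0 = 27.8 points. The error can go either way.

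**The case against.** A reader might infer that follow-up ends in exactly those patients in whom drug withdrawal has failed, so that the trial is bound to make withdrawal look safe. The Protocol does not support that. Failure of withdrawal is the primary endpoint: worsening signs or symptoms alone can qualify (4.3.1), and the stated response is to restart treatment, with no mention of removal (4.4.1). A heart failure hospitalisation is itself a recorded outcome, and later removal does not erase it. The removal grounds apply to both arms, a serious adverse event may have nothing to do with the heart, and poor adherence may mean missed visits or a continuation-arm patient stopping drugs. Much drug resumption in the withdrawal arm is expressly allowed (4.4.3).

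Nor does follow-up simply stop. Part (3) of 4.2.3.1 asks for every effort at contact and does not rule out a month-6 assessment, and section 10.1.2 keeps adverse events followed until they resolve or stabilise. Exclusion from the analysis is only one reading, and the SAP, which was not available, may settle it. Losing three deteriorations undocumented is also a severe case, given monthly NT-proBNP and echocardiography.

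All of this stands and limits the claim. It does not supply a schedule: following an adverse event to resolution is not the monthly endpoint assessment, and an assessment that is merely possible is not required.

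**Conclusion.** The point holds in a limited form. Section 4.2.3 merges stopping the strategy with leaving the study, gives an unblinded investigator grounds for removal that can depend on outcome and arm, and does not keep removed patients on the schedule to month 6. This sits badly with the 6-month follow-up of all participants in section 4.1. It can bias the primary endpoint and lose 6-month secondary data; it need not, and the direction is not fixed.

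The firm figure is 4% of an arm per patient. The loss of 8 to 12 points for three undocumented events rests on assumed counts (5 to 10 of 25 versus 0 or 1 of 25) and on all three losses falling in the drug-withdrawal arm. Such a loss moves the Fisher p above 0.05 in some scenarios (7 vs 1, 8 vs 1, 6 vs 0) but not in others (10 vs 1). No figure stated in the Protocol is contradicted. This is a cheap improvement, not a defect that invalidates the design.

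**What to change.** Amend section 4.2.3 to say that:
1. A serious adverse event, a complication or physiological change, or poor adherence may end the assigned strategy but does not end outcome follow-up. Treatment decisions stay as the Protocol already leaves them.
2. Every randomised patient who has not withdrawn consent for follow-up stays on the existing visit schedule to month 6, including the CMR and KCCQ.
3. Poor adherence is no longer a reason for removal from the study. It is recorded and reported, which a feasibility pilot needs in any case.
4. Patients whom the investigator takes off the strategy are not classed as lost to follow-up on that ground, and are analysed in their randomised arm.

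The cost is an amendment with ethics approval, plus the remaining scheduled visits for a few more patients. The Protocol states funding only for the 6-month CMR and echocardiography (7.1, 8.3), so cover for the monthly visits should be confirmed. No new procedure and no change in sample size is needed.

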##### **(2) Withdrawal Initiated by the Participant**

a) The participant, for any reason, is unwilling or unable to continue the clinical trial and requests termination of participation;

b) The participant does not explicitly request withdrawal but discontinues treatment and follow-up, resulting in loss to follow-up.

##### **(3) Handling of Withdrawn Cases**

For all withdrawn cases, the status of clinical trial completion and the reasons for withdrawal should be documented. After a participant withdraws, the investigator should make every effort to contact the participant, inquire about the reason for withdrawal, record the most recent clinical symptoms, and complete any assessments that can still be performed. If withdrawal is due to an adverse event, the investigator should provide appropriate medical management based on the participant's condition.

When a participant or their legal guardian requests withdrawal from the trial, the investigator should ask whether previously collected data may still be used for the clinical study, and the response should be documented in the raw records.

### **4.3 Study Outcomes**

#### **4.3.1 Primary Endpoint**

HF deterioration within 6 months.

Defined as meeting any of the following criteria:

(1) A decrease in LVEF on echocardiography by >10% in absolute value and to <55%;

- (2) An increase in LVEDD on echocardiography by >10% and exceeding the normal range;
- (3) A twofold rise in NT-proBNP and to >400 ng/L;
- (4) None of the above criteria are met, but worsening HF signs and/or symptoms are present,, as adjudicated by the research team.

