## **4. Study Design**

### **4.1 Overall Design**

This trial is a single-center, open-label, pilot, randomized controlled trial designed to assess the feasibility of conducting a large-scale investigation. The study will enroll patients with AF and HF who demonstrate improvement in cardiac function after catheter ablation.

Patients who sign an ethics committee–approved informed consent form and are deemed eligible for enrollment by the investigators may be included in the study. After enrollment, participants will be randomized 1:1 to phased GDMT withdrawal or continuation using computer-generated sequences via SAS software. The physicians responsible for enrollment and assignment of participants were blinded to the random allocation sequence. The experimental group will undergo stepwise withdrawal of GDMT, while the control group

will continue GDMT. All participants will be followed for 6 months to compare the safety and efficacy outcomes between the two groups.

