#### **4.6 Imaging Assessment Methods**

##### **4.6.1 Echocardiography Protocol**

Echocardiography was performed by experienced operators from the same echocardiography team using a commercially available system (Epic 7c, Philips Healthcare, Best, The Netherlands) equipped with a 3.5 MHz transducer for 2-dimensional imaging. All measurements were conducted in accordance with current guideline recommendations. LVEDD and left ventricular end-systolic diameters were manually traced at end-diastole and end-systole in both apical 4- and 2-chamber views. LVEF was calculated using the modified Simpson's biplane method. LA diameter was measured using the biplane method from apical views. Diastolic function was evaluated by measuring the mitral inflow E/A ratio and deceleration time of mitral inflow. In addition, tissue Doppler imaging was performed in the apical 4-chamber view. Peak systolic (S'), early diastolic (E') velocities of the medial and lateral mitral annulus, and the corresponding E/E' ratio were calculated. Sector width and

imaging depth were optimized individually to ensure the highest achievable frame rate and the optimal visualization.

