#### **4.6.2 Cardiac Magnetic Resonance Scan Protocol**

CMR scans were performed on a 3-Tesla MR scanner (Ingenia CX, Philips Healthcare, Best, The Netherlands) with a 32-channel phased-array coil and a retrospective ECG gating. The CMR protocol comprised a standardized protocol including balanced steady-state free precession sequences for left ventricle cine images (short axis, 2, 3, 4 chambers), and Modified Look-locker inversion recovery (MOLLI) sequences for both pre- and post-contrast T1 mapping images, and late gadolinium enhancement images (LGE). LGE imaging was implemented 10 min after intravenous administration of contrast medium (0.2 mmol/kg; Magnevist gadopentetate dimeglumine, Bayer Healthcare, Bayer, Berlin, Germany) using a phase-sensitive inversion-recovery (PSIR) TFE sequence. General CMR analyses (cardiac function, myocardial strain, extent and distribution of LGE, T1 mapping) were conducted using the CVI 42 software (Circle Cardiovascular Imaging, Calgary, Canada) by a radiologist who was blinded to treatment allocation.

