## **8.2 Quality Control of Imaging Examinations**

To ensure the quality of echocardiography and CMR, the same sonographer and CMR physician will perform all examinations on the same equipment for each patient, minimizing bias.

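### Three of the four criteria that can each trigger the primary endpoint have no stated masking in this open-label trial; the threshold-free criterion 4 is the most exposed

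*Protocol*

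**What the plan says.** Section 4.1 describes the design: "This trial is a single-center, open-label, pilot, randomized controlled trial". The primary endpoint in 4.3.1 is HF deterioration within 6 months, met by any one of four criteria:

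1. "A decrease in LVEF on echocardiography by >10% in absolute value and to <55" percent.
2. "An increase in LVEDD on echocardiography by >10% and exceeding the normal range".
3. NT-proBNP doubled and above 400 ng/L.
4. Worsening HF signs and/or symptoms when none of the first three is met, "as adjudicated by the research team".

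On echo, 4.6.1 says: "Echocardiography was performed by experienced operators from the same echocardiography team". It describes manual tracing and does not mention what the operators know about treatment. Section 8.2 adds that "the same sonographer and CMR physician will perform all examinations on the same equipment for each patient". On CMR, 4.6.2 says the analyses are done "by a radiologist who was blinded to treatment allocation"; under 4.3.2, CMR enters only the secondary endpoints. The one other use of the term is in 4.1: "The physicians responsible for enrollment and assignment of participants were blinded to the random allocation sequence". That is allocation concealment, not masked outcome assessment. Section 4.7 (Bias Control) covers the prospective design, training and eligibility, and does not mention outcome assessment.

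**The concern.** The protocol states masking for an imaging method behind secondary endpoints and leaves it unstated for the echo measurements and the clinical judgement behind the primary endpoint. Criterion 4 combines three weaknesses: it applies only when no measured criterion is met, it has no threshold, and nothing keeps staff who know the arm from deciding it. HF medications are recorded at every visit (4.5.1), so some of the research team will know the arm.

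Echo and NT-proBNP are repeated monthly, so there are six follow-up occasions on which a criterion can be met. Extra vigilance for withdrawn patients would add events to the withdrawal arm. An expectation that withdrawal is safe would remove them, in a trial whose objective includes safety. Section 4.4.1 also links GDMT re-initiation to occurrence of the primary endpoint, so an arm-dependent call can change later treatment exposure as well as the event count. Later analysis cannot fully undo that, and who assesses and what they may know is a matter of conduct that belongs in the protocol.

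**Working it through.** **1. Masking by component (Protocol)**

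| Item | Nature | Masking stated? |
|---|---|---|
| Criterion 1, LVEF (4.3.1, 4.6.1) | manual echo tracing | no |
| Criterion 2, LVEDD (4.3.1, 4.6.1) | manual echo tracing | no |
| Criterion 3, NT-proBNP (4.3.1) | laboratory value | little need |
| Criterion 4, signs/symptoms (4.3.1) | judgement, no threshold | no |
| CMR measures (4.3.2, 4.6.2) | secondary endpoints | yes |

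**2. Weight of one call**

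Inputs: 25 per arm (Protocol Summary); two-sided 0.05, chi-squared or Fisher's exact test (5.3.2).

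One call = 1/25 = 4 percentage points. With no control events and *a* withdrawal events, Fisher's two-sided p = 2 × C(25,a)/C(50,a):

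- a = 5: 2 × 53,130 / 2,118,760 = 0.0502
- a = 6: 2 × 177,100 / 15,890,700 = 0.0223

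So a sixth event takes the result across 0.05. With one control event, seven are needed (p = 0.049).

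**3. Arm-dependent calls with no true difference**

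Assume the same true risk p in both arms, and that a fraction x of event-free withdrawal patients is wrongly called an event. The apparent withdrawal risk is q = p + (1 − p)x, and the extra events are 25(q − p). For p = 0.10 and x = 0.10, q = 0.19 and the extra events are 2.25. Exact binomial enumeration with 25 per arm gives these probabilities of a significant result:

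| True risk p | x | Extra events | Fisher | Chi-squared (uncorrected) |
|---|---|---|---|---|
| 5% | 0 | 0 | 0.001 | 0.020 |
| 5% | 10% | 2.4 | 0.063 | 0.198 |
| 10% | 0 | 0 | 0.009 | 0.049 |
| 10% | 10% | 2.25 | 0.071 | 0.153 |
| 20% | 0 | 0 | 0.022 | 0.055 |
| 20% | 10% | 2.0 | 0.052 | 0.107 |

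Here p and x are assumptions; the protocol gives no event rates.

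**4. Arm-dependent echo reading, criterion 1 only**

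Assume stable patients with true LVEF of mean 60 and SD 4, reading = true value + error of SD s, and a reference reading of at least 55%. A false event is a reading more than 10 points below the reference and below 55% at any of six visits. In one arm every follow-up reading is 2 points lower. Simulated false-event rates:

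| Reading SD s | No shift | 2-point shift | Difference | Patients in 25 |
|---|---|---|---|---|
| 2 | 0.1% | 0.9% | 0.8 points | 0.2 |
| 2.5 | 0.8% | 4.2% | 3.4 points | 0.9 |
| 3 | 3.1% | 10.1% | 7.0 points | 1.8 |
| 4 | 12.4% | 25.2% | 12.8 points | 3.2 |

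The spurious difference is therefore about 1 to 13 points, governed mainly by the reading SD. A higher true mean makes it smaller. Readings shifted upward would remove events instead.

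**The case against.** **Silence is not a statement.** A reader might infer that the echo operators and adjudicators are unblinded. The protocol does not say so; it does not say what the operators know or which team members adjudicate. What stands is that masking is not stated where it matters most, in an open-label trial that does state it for CMR.

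**The endpoint is partly protected.** It would be wrong to say that it rests only on echo and judgement. NT-proBNP is objective and measured monthly. Criteria 1 and 2 each need two conditions together, which blunts small reading shifts. That is right, but any single criterion makes an event, and criterion 4 has no such guard.

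**The echo effect may be small.** A reader might take the upper rows of the last table, 7 to 13 points, as the size of the bias. They depend on assumed reading SDs of 3 to 4. The same-sonographer, same-equipment rule in 8.2 is meant to keep variability low, and at SD 2 to 2.5 the difference is about 1 to 3.5 points. Even the SD 3 and SD 4 rows would make Fisher's test significant in only about 2% and 13% of trials. This stands, and it is why criterion 4 comes first. One might also fault 8.2 because the same sonographer could remember earlier values; the documents do not show that this happens, and the rule has a clear purpose.

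**It is a pilot.** No power is claimed (5.1), and blinded CMR LVEF at 6 months gives a partial check on echo LVEF. But CMR cannot check events at earlier visits or criterion 4, and 5.3.2 formally tests the primary endpoint.

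**Masked re-reading is costly.** A second reader would face 50 × 6 = 300 follow-up echoes and would create two LVEF values per visit. That is a fair objection to re-reading, not to masking the existing operators.

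**Conclusion.** The concern holds as a gap in the protocol: three of the four triggering criteria have no stated masking. Criterion 4 is the most exposed, at 4 percentage points per call, in a trial where 0 versus 6 events reaches significance by Fisher's test. These two figures need only the 25 per arm and the 0.05 level.

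The other sizes are illustrations. About two wrongly called withdrawal patients raise the false-positive rate to roughly 0.05–0.07 (Fisher) or 0.11–0.20 (uncorrected chi-squared) at assumed true risks of 5–20%. A 2-point LVEF reading shift adds about 1 to 13 points of false events at assumed reading SDs of 2 to 4. No document figure fixes the reading SD, the shift, the LVEF distribution or the true risk. The direction is unknown, so the documents do not support a claim that the trial favours either arm, or that assessors are in fact aware of the allocation.

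**What to change.** - **4.3.1:** state that criterion 4 is adjudicated by existing team members who are not treating the patient, from packets with arm and HF drugs removed.
- **4.6.1:** state that the existing echo operators measure LVEF and LVEDD without knowledge of arm or HF drugs, as 4.6.2 already states for CMR. This keeps the same-sonographer rule in 8.2 and needs no second reading. If the operators are already masked, one sentence settles it.
- **4.3.1 and 4.4.1:** state that the masked classification defines the primary endpoint for analysis, and reconcile this with the sentence in 4.4.1 that ties GDMT re-initiation to the primary endpoint, so that the two sections cannot be read as using different events. How treatment decisions are made is for the investigators.

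**Cost:** protocol wording, packet preparation for a trial of 50 patients, and some delay in endpoint classification. No new personnel, scans or change in sample size.

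**What remains:** patients know their treatment, so their own symptom reporting stays unmasked. The change removes only the assessors' share of the bias.
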